### 2.4. Sample Size Determination

Based on previous studies [15], and assuming the BF suspension rate at 6 months to be 60% in the control group versus 40% in the intervention group, with a significance level of *p* < 0.05 and a statistical power of 85%, a balanced design would require 333 women in total. Compensating for an estimated loss rate of 20%, the estimated final total sample size would be 399 women.

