## Abstract

Purpose: The primary aim of this study is to determine the influence of an intervention in women based on a free mobile application (LactApp^®^, Barcelona, Spain) in maintaining breastfeeding (BF) up to 6 months postpartum. The secondary aim is to assess the effect of health literacy (HL) on breastfeeding duration. Methods: A multicenter, randomized controlled clinical trial of parallel groups will be carried out. Women will be randomly assigned to each of the parallel groups. In the control group, usual clinical practice will be followed from the third trimester of pregnancy to promote BF. In the intervention group, and in addition to usual clinical practice, the women will use a free mobile application (LactApp^®^) from the third trimester to 6 months postpartum. The type of BF at birth, at 15 days and at 3 and 6 months postpartum and the causes of cessation of BF in both groups will be monitored. The hypothesis will be tested using inferential analysis, considering an alpha of 5%. The study protocol was approved by the Clinical Research Ethics Committee of Hospital de la Ribera (Alzira, Valencia, Spain) in February 2021. A per protocol analysis and an intention-to-treat analysis will be performed. Discussion: This study will identify the influence of a mobile application on improving BF rates. If the application proves effective, we will have a tool with free information available to any user at any time of day, which may be complemented by normal clinical practice and be integrated into our health care system. Trial registration: ClinicalTrials.gov ID: NCT05432700.

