#### 2.8.2. Secondary Outcome

The level of HL (adequate vs. inadequate) with the HLS-EU-Q16 screening tool and the characteristics of the women who gave up BF at 6 months (yes/no) will be assessed via two-input tables with application of the chi-square test (χ^2^) for qualitative variables. Multivariate logistic models will be used in order to analyze the magnitude of the association with BF at 6 months. The adjusted odds ratio (OR) and 95% confidence interval (95%CI) will be calculated, and *p*-values will be presented.

Data analysis will be performed using SPSS v.26.0 for Windows (IBM Corp. 2018, Armonk, NY, USA) and R (R project 2019, version 4.0.2). The level of statistical significance defined was *p* < 0.005.

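### Section 2.4 states 333 women (399 with losses), but its own inputs give 222, and 399 less 20% leaves 319; at alpha 0.05 the error is conservative

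*Protocol article*

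**What the plan says.** Section 2.4 sets power at 85% and alpha at 0.05, and takes suspension of breastfeeding at 6 months to be "60% in the control group versus 40% in the intervention group". From these inputs it concludes that "a balanced design would require 333 women in total". It then allows for a 20% loss rate and states that "the estimated final total sample size would be 399 women".

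Other sections supply what else is needed. Section 2.3 describes two groups, control and intervention, of equal size. Section 2.8.1 names the chi-square test for suspension of breastfeeding at 6 months. The Abstract agrees with section 2.4 on an alpha of 5%. Section 2.8.2 does not: "The level of statistical significance defined was *p* < 0.005". Whether the test is one- or two-sided is not stated.

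**The concern.** Section 2.4 prints every input to a standard two-proportion calculation, so the result can be checked directly. A 20-point difference centred on 50% at 85% power is a familiar case, and 333 is well above what it requires. The step from 333 to 399 also looks like multiplication by about 1.2, which does not preserve 333 after a 20% loss.

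The size, the power and the loss allowance cannot all be true together. A reader would take the trial to have 85% power for a 20-point difference, and would not learn what difference the planned sample can detect. An ethics committee could not tell whether the rates, the power or the total was the intended figure.

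**Working it through.** **Inputs.** Control 0.60 and intervention 0.40 (2.4), so the difference is 0.20 and the mean 0.50. Alpha 0.05 (2.4 and Abstract), taken as two-sided. Power 85% (2.4). Two equal arms (2.3, 2.4). Chi-square test (2.8.1). Loss 20% (2.4).

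**Step 1: trying to reproduce 333.** The pooled-variance formula is

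n per arm = [z(1−α/2) × √(2 × p̄ × (1−p̄)) + z(power) × √(p1(1−p1) + p2(1−p2))]² / (p1−p2)²

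= [1.960 × √0.50 + 1.036 × √0.48]² / 0.04 = 110.7, so 111 per arm and **222 in total**.

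Other choices at alpha 0.05 and 85% power:

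| Variant | Total |
|---|---|
| Two-sided, pooled | 222 |
| Two-sided, continuity-corrected (120.5, so 121 per arm) | 242 |
| Two-sided, unpooled | 216 |
| Two-sided, arcsine | 222 |
| One-sided (with continuity correction) | 178 (198) |
| Two-sided, 2:1 allocation (with continuity correction) | 249 (273) |

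None comes within 3% of 333. The excess is 333/222 = 1.50, or 333/242 = 1.38 and 333/216 = 1.54 at the ends of the two-sided 1:1 range.

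**Step 2: the loss allowance.**

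- 399 × 0.8 = 319.2, so about 319 evaluable, 14 short of 333.
- 333/0.8 = 416.25, so 417 would have to be randomised to keep 333.
- 399/333 = 1.198 and 333 × 1.2 = 399.6, which fits multiplication by 1.2.
- 1 − 333/399 = 16.5%: the only loss rate at which 399 leaves 333.
- From the requirement that does follow: 222/0.8 = 277.5, so 278; 242/0.8 = 302.5, so 303.

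**Step 3: what the planned size delivers for 60% versus 40%, at two-sided 0.05.** The same formula is solved for power, without continuity correction.

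| Evaluable women | Power |
|---|---|
| 222 | 85.1% |
| 319 | 95.0% |
| 320 | 95.1% |
| 333 | 95.8% |
| 399 (no loss) | 98.1% |

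For 320, that is 160 per arm: (0.20 × √160 − 1.960 × √0.50)/√0.48 = 1.651, and Φ(1.651) = 0.951. Solving instead for the difference detectable with 85% power from a 60% control rate gives about 16.7 points with 319 or 320 evaluable.

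**Step 4: the other significance level.** At two-sided 0.005 (z = 2.807), 85% power for 60% versus 40% needs 183 per arm, 366 in total (386 with continuity correction). Power is 80.5% with 333 evaluable and about 78% with 319 or 320. For 320: (0.20 × √160 − 2.807 × √0.50)/√0.48 = 0.787, and Φ(0.787) = 0.784.

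**The case against.** The strongest reply is that no harm follows. The 399 planned exceeds the correct requirement after loss (278, or 303 with continuity correction), and even 319 evaluable is well above 222. This stands, and it limits the severity. A reader who sees two errors in a sample-size paragraph might infer that the trial is underpowered, or that it must recruit 417. The document supports neither at alpha 0.05: 417 protects a figure of 333 that the inputs never required.

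A second reply is that another input was used. Changing one does bring the total near 333: two-sided 0.005 at 80% power gives 330, one-sided 0.005 at 85% gives 324, and two-sided 0.05 at 95% with continuity correction gives 340. None equals 333, and each contradicts section 2.4. Nor can one infer from section 2.8.2 that the trial was sized at 0.005. Two-sided, that needs 366, and the Abstract and section 2.4 agree on 5%.

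A third point concerns the cause. It is tempting to note that 333 = 3 × 111 and conclude that the calculation was made for three groups. That is a guess: the document mentions only two groups, and the finding does not depend on the explanation. The multiplication by 1.2 is likewise inferred from the ratio of the two totals.

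Finally, 222 is not the only defensible answer, because section 2.4 states neither sidedness nor continuity correction. This also stands, so both 222 and 242 are given. It does not rescue 333.

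**Conclusion.** Both arithmetic faults hold. The inputs of section 2.4 require 222 evaluable women (242 with continuity correction), not 333. A total of 399 with a 20% loss leaves 319, not 333. At two-sided 0.05 the planned size gives about 95% power for the assumed difference, so 85% understates the power and the error is conservative.

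The conclusion rests on the stated rates, two equal arms, a two-sided test at 0.05 and a loss of exactly 20%. It does not carry over to p < 0.005, where about 320 evaluable women fall short of 85% power. The conflict between sections 2.4 and 2.8.2 therefore decides which power statement is true. Severity: should be fixed. It is a wrong statement of size and power, but it does not endanger the primary comparison at the level section 2.4 uses.

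**What to change.** Rewrite section 2.4, keeping recruitment at about 400:

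1. State that 60% versus 40%, two-sided alpha 0.05 and 85% power require 222 evaluable women (111 per arm), or 242 (121 per arm) with continuity correction. Say which method is used.
2. Allow for loss by dividing by 0.8, which gives 278 (or 303) to be randomised.
3. State what the planned size delivers: about 400 randomised leaves about 320 evaluable after 20% loss. At two-sided 0.05 that gives about 95% power for 60% versus 40%, or 85% power for a difference of about 17 points from a 60% control rate.
4. Make these figures explicitly conditional on alpha 0.05, and reconcile that level with the p < 0.005 in section 2.8.2.

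If 0.05 is confirmed, the cost is a text correction with no change to recruitment. If 0.005 is the intended level, the power statement must instead read about 78%. Keeping 85% power would then need 366 evaluable women, which about 400 randomised would not provide after a 20% loss.

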### 2.5. Intervention

#### 2.5.1. Both Groups

The study sample will be compiled during the third trimester of pregnancy in the different primary care midwife consulting rooms of each of the participating centers. After receiving the envelope, the women will read the QR code with their mobile device and will be registered in the nursing platform created for the study, after accepting the privacy policy statement. Both the intervention group and the control group will undergo an initial survey to record sociodemographic data, previous experience with BF, and the probable date of delivery. In addition, two self-administered questionnaires will be completed—one on HL (HLS-EU-Q16) [34] and another on health-related quality of life (EQ-5D-5L) [35]—through the e-mail account registered on the platform.

Planning of reminders via e-mail will be performed to obtain information referred to follow-up, at all times avoiding the provision of any extra information on BF. During pregnancy, based on the pregnancy protocol and usual clinical practice, parent role education and nursing workshops will be planned for both groups, with the availability of different manuals to be given to each pregnant woman [36].

The platform will send serial e-mails to both study arms (intervention and control) for follow-up on the type of nursing after birth, at 15 days, at 6 weeks, and at 3 and 6 months. Questions will be asked regarding the type of nursing and BF-related problems, and the breastfeeding self-efficacy scale—short form (BSES-SF) will be applied [37]. In the event of the suspension of BF, the reason for suspension will be recorded, along with the total breastfeeding time. At 3 and 6 months postpartum, new measurements will be made with the health-related quality of life questionnaire (EQ-5D).

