### 2.3. Randomization and Blinding

The women will be included during the third trimester of pregnancy in the different primary care midwife consulting rooms of each of the participating centers. After reading the information sheet and giving informed consent, the women will be registered on a webpage created for the purpose of the research and will be assigned to one of the groups (control or intervention) via a simple randomization process, until the estimated sample size has been reached. Randomization will be performed using Epidat v.4.2. [33], with groups of equal size.

Allocation concealment will be carried out, with blinding of the midwives in charge of recruiting the women, providing them with sealed, opaque and sequentially numbered envelopes to be delivered to each new participant wishing the participate in the study.

The research team will prepare the envelopes based on the random allocation sequence. Each envelope will contain a card with a QR code providing access to the study follow-up platform. Follow-up data collection will be conducted by another researcher blinded to the group status of participants. Only the data manager will have access to all of the integrated data (the data reported by the participating women through the surveys and the birth/postpartum data reported by the principal investigators).

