#### 2.5.3. Intervention Group (Mobile Application Group)

From the first recording during the first trimester, the women will be able to consult all the available information in the application. LactApp^®^ is a free access mobile application developed through Apple Store and Google Play, and can be consulted in English and Spanish [38,39]. The central function of LactApp^®^ is its automated nursing consultation structure. This tool also uses artificial intelligence and is available 24 h a day with a connection to the Internet, providing convenient and personalized support. LactApp^®^ includes a self-management form based on over 50 decision trees with questions and answers developed by nursing experts, and is supported by scientific evidence and current official health recommendations. The questionnaire generates over 2300 personalized replies that can be reached through over 76,100 potential routes that vary fitting to the profile of the users and the options selected by the latter. In addition, the application reminds the user about the following issues, depending on the entered date of birth:The first four weeks: positioning of the infant for breastfeeding, frequency of milk intake, number and consistency of stools, general care of the breast, and weight gain of the newborn. For women providing food supplements, the tool offers counseling and support for returning to breastfeeding.From months two to three: recommendations on milk extraction to create a reserve in case of having to return to work or leave home, with instructions on handling and storage of the collected milk.From months four to six: how to use the milk reserve (if any) and techniques for administering the stored milk, placing emphasis on the importance of supporting BF and the advisability of not using other types of feeding.

If the intervention is effective and differences are found between the two groups, an analysis will be conducted within the intervention group to analyze the profile of women who are less likely to abandon BF at 6 months based on baseline variables, by adjusting a multiple logistic regression model, estimating the corresponding ORs and 95%CIs.

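### Section 2.5.1 collects the self-reported baseline measures after the allocation envelope, section 2.3 reads as registration before assignment, and nothing requires completion before the arm is known

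*Protocol article*

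**What the plan says.** Section 2.3 (Randomization and Blinding) says that after consent "the women will be registered on a webpage created for the purpose of the research and will be assigned to one of the groups" by simple randomization. It adds: "The research team will prepare the envelopes based on the random allocation sequence". On their content: "Each envelope will contain a card with a QR code providing access to the study follow-up platform".

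Section 2.5.1 (Both Groups) gives another sequence: "After receiving the envelope, the women will read the QR code with their mobile device and will be registered in the nursing platform". Then, "Both the intervention group and the control group will undergo an initial survey to record sociodemographic data, previous experience with BF", together with the probable date of delivery. HLS-EU-Q16 and EQ-5D-5L are self-administered "through the e-mail account registered on the platform".

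Section 2.5.3 states when the app opens to the intervention arm: "From the first recording during the first trimester, the women will be able to consult all the available information in the application". (The trimester named there differs from the third trimester given elsewhere. That is a separate inconsistency, also to be reconciled.)

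Section 2.7 lists the sociodemographic items, HLS-EU-Q16 and EQ-5D among the variables collected at baseline.

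**The concern.** A baseline variable is protected by randomization only if it is measured before the participant can react to her arm. In the section 2.5.1 order, the envelope that carries the allocation comes first and all self-reported measures come later, two of them by e-mail. App access starts at the first recording, with no condition that the questionnaires be finished.

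HLS-EU-Q16 asks how easy a woman finds it to handle health information, and EQ-5D-5L asks how she feels on the day. Both are self-rated, so both could shift in a woman who knows she has been given an information app or has begun to use it. Willingness to complete the forms could also differ by arm.

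Four analyses depend on these measures being true baseline:

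- the secondary analysis, in which health literacy is the exposure (section 2.8.2);
- the adjusted models, which take in any poorly distributed characteristic (section 2.10);
- the model profiling women within the intervention group from baseline variables (section 2.5.3);
- the comparison of baseline characteristics between losses and completers (section 2.8), on which section 4 relies, together with the intention-to-treat analysis, to control selection bias.

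The adjustment rule adds a particular difficulty. If the arm shifts a self-rated score, the shift appears as imbalance and can bring that score into the model. The model then adjusts for a consequence of allocation and may remove part of the app's effect.

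**Working it through.** The point rests on the order of procedures, so the main check is to set the sections side by side.

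| Step | Section 2.3, sentence order | Section 2.5.1 |
|---|---|---|
| 1 | Consent | Envelope received |
| 2 | Registration on a study webpage | QR code read |
| 3 | Assignment to a group | Registration on the platform |
| 4 | – | Initial survey, described by group |
| 5 | – | HLS-EU-Q16 and EQ-5D-5L by e-mail |

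1. The envelopes are made up from the random sequence, so the arm is fixed once an envelope is handed over. Steps 2 to 5 of section 2.5.1 all follow allocation.
2. Section 2.3 itself puts the QR card inside the envelope. If the card is the route to registration, registration cannot precede the envelope, and the sentence order of section 2.3 cannot hold. If the webpage and the platform are two systems, the two orders of registration can both be true, but all questionnaires still follow the envelope.
3. Neither section says when the woman learns her arm. Section 2.5.3 opens the app from the first recording and does not make completion of the questionnaires a condition.
4. Items differ in exposure. Age and education cannot change with the arm. Self-rated health literacy, EQ-5D-5L and the decision to respond can.
5. The primary chi-square test (section 2.8.1) uses no baseline variable. It is touched only through the set of women counted.

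**Scale, on assumptions only.** The documents give no rate of non-registration or non-response at baseline. If 5% to 10% of the 399 planned women lacked baseline data, that would be 0.05 × 399 ≈ 20 to 0.10 × 399 ≈ 40 women missing from a complete-case adjusted model.

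**A difference in loss is not a bias of the same size.** Take the planned suspension rates from section 2.4, 40% (app) and 60% (control), and assume losses of 10% and 5%.

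- Suppose suspension is 20 points higher in lost than in retained women. The retained rate is then p − L × 0.20, where p is the planned rate and L the loss. App: 0.40 − 0.10 × 0.20 = 0.38. Control: 0.60 − 0.05 × 0.20 = 0.59. The difference is 21 points, so the bias is 1 point.
- Suppose every lost woman suspends. The retained rate is then (p − L)/(1 − L). App: 0.30/0.90 = 33.3%. Control: 0.55/0.95 = 57.9%. The difference is 24.6 points, so the bias is 4.6 points.

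The same 5-point difference in loss thus gives a bias of 1 to 4.6 points in these two cases, depending on how the lost women differ. The documents do not fix this.

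**The case against.** The strongest reply has four parts.

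- **The conflict is one of wording.** Section 2.3 joins registration and assignment with a plain conjunction, the webpage and the platform may be two systems, and the flowchart (Figure 1) is not shown. This stands as far as the conflict goes. It does not alter the section 2.5.1 order, which places every questionnaire after the envelope.
- **Disclosure before baseline is not stated.** The only stated content of the envelope is a card for a platform that both arms use, and the platform could show the arm after the surveys. This stands. A reader might infer that women do know their arm when they answer; the documents do not say so. The supported statement is that nothing prevents it.
- **Losses can be traced.** A reader might infer that women who take an envelope and never register disappear from view. The text does not support that. Envelopes are sequentially numbered (section 2.3), losses and their causes are to be detailed (section 2.6), and the intention-to-treat analysis covers all randomized subjects and assigns lost women the outcome least favourable to the app (section 2.8). What remains open is whether an unregistered envelope-holder counts as randomized. She would also have no survey data for the comparison of losses with completers.
- **The analytic harm is speculative.** Section 2.10 does not name health literacy among the factors that may influence the results, and the gap before an e-mailed form may be short. This limits the likely size. But the section 2.10 rule admits any poorly distributed characteristic, and health literacy is the exposure of the secondary aim.

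**Conclusion.** The point holds in a limited form and should be corrected. As section 2.5.1 is written, all self-reported baseline measures follow allocation. Section 2.3 reads differently, and no stated safeguard keeps the measures ahead of arm disclosure or app access. Health literacy, EQ-5D-5L and the pattern of completion can therefore be affected by the arm. That weakens the secondary analysis, the adjusted models triggered by imbalance, the profile model within the app arm, and the comparison of losses with completers.

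The unadjusted primary test is not threatened unless envelope-holders who never register are left out of the randomized set.

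The size cannot be stated from the documents. It would be tempting to set a 5-point difference in loss against the planned 20-point effect and call it a quarter of that effect. That is not valid: a difference in loss and a difference in outcome are not on one scale, and the worked cases show how far the resulting bias depends on assumed differences between lost and retained women. The conclusion assumes only that the procedure follows section 2.5.1 as written and that disclosure is not delayed by a step the article does not describe.

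**What to change.** Reconcile sections 2.3 and 2.5.1 to one order: consent, registration, initial survey, HLS-EU-Q16 and EQ-5D-5L, and only then envelope opening or disclosure of the arm. Completing the two questionnaires at enrolment, not later by e-mail, would achieve this.

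State in section 2.8 that every issued envelope number belongs to the set of all randomized subjects in the intention-to-treat analysis, whether or not the code is scanned.

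The cost is a short wording change, a platform setting and a few more minutes at enrolment. The change has to come before recruitment, because a measure taken after disclosure cannot be turned back into a baseline measure in the analysis. If some women have already been enrolled in the section 2.5.1 order, record when each completed the questionnaires relative to disclosure and first app use, and report this with the health-literacy results.
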